#### HEG group

3.2.2

Participants in this group will be advised to adhere to the current Irish Healthy Eating Guidelines [42] with particular emphasis on portion sizes, low fat options and healthy cooking methods. The current Healthy Food for Life – the Healthy Eating Guidelines and Food Pyramid have been developed by the Department of Health in Ireland. The food guide consists of a pyramid representing how different foods and drinks contribute towards a healthy balanced diet. Participants will be advised to limit foods that are high in fat, sugar, and salt to no more than once or twice a week. The diet also emphasizes the consumption of 5–7 portions of fruits and vegetables per day. All participants will be provided with resources to inform them of these guidelines and sample meal plans that are readily available on the Healthy Ireland website (HSE, http://www.hse.ie). A copy of the 101 Square Meals book from Safefood Ireland will be provided to participants in this group. The book includes shopping tips, food safety messages, menu planning advice as well as some healthy treats and snacks ideas. The book uses the Healthy Food for Life Guidelines to help individuals plan healthier meals and will help participants to have a varied and healthy diet while getting the best value for their money.

The diet will be modified and tailored to the participant's preferences by the study RD. This is first achieved based on the assigned diet and overarching principles, however within this, the RD works with the participants on a personal level to ensure the dietary recommendations were achieved. For example, if a person didn't like a recommended food, an alternative of equal nutritional value will be recommended based on participants' preferences. The RD will also manage participants who have allergies to specific food and food components. In the case of food allergies, the RD will evaluate and ensure the nutritional adequacy of an allergen-free diet and suggest appropriate substitutions or individual food replacements.

### Focus groups

3.3

Semi-structured focus groups from each intervention arm will be conducted at the end of study period. The focus groups will aim investigate participants’ experiences in the MEDRA study and explore the self-perceived enablers and barriers towards adhering to the dietary intervention. A moderator who is a member of the research team but not involved directly with the participants will facilitate the semi-structured focus groups of approximately 4–5 people in an open discussion. Open-ended questions will be asked to encourage the participants to express their views openly and spontaneously. Each focus group will last around 50–60 min and will be audio recorded.

## Outcome measures

4

The outcome measures and their corresponding timelines are presented in Table 1. Primary outcome measures include physical function and quality of life. Patient information including demographic data, smoking status, medication and supplement consumption are collected at baseline and any changes or additions in pharmacological treatment will be noted during the study period.

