**Methods:**

The MEDRA study is a parallel, randomised controlled trial delivered through telehealth methods. Forty-four eligible participants who have RA will be randomly allocated to either a MedDiet or HEG group for a 12 weeks intervention period. Primary outcome measures include changes in physical function and quality of life, both of which will be measured using validated questionnaires at baseline, six and twelve weeks. Both intervention arms will attend a total five teleconsultations with a Registered Dietitian (RD). The MedDiet intervention arm focuses on recommendations from the traditional Mediterranean diet and HEG intervention arm will use the dietary recommendations as currently advised in Ireland.

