### Study design

2.1

The MEDRA study is a 12-week, parallel group, randomised controlled trial comparing two dietary interventions for the management of RA. This trial is designed in accordance with and adheres to the Consolidated Standards of Reporting Trials (CONSORT) statement [30]. Study participants will be randomly allocated to either a MedDiet group or the HEG group. Participants from both arms will attend five teleconsultations in total with the study Registered Dietitian (RD) over the 12-week intervention period on weeks 0, 3, 6, 9 and 12. For this study, blinding to intervention will not be possible but every effort will be made to manage participants in both groups as equally as possible. The primary endpoint is an improvement in physical function and quality of life of participants over the study period. The study design is detailed in Fig. 1.

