### Physical function and quality of life

4.1

The Rheumatoid Arthritis Quality of Life instrument (RAQoL) is the first patient-completed instrument specifically designed for use with people with RA. It entails 30 questions and respondents are required to indicate whether each of the questions applies to them. Scores range from 0 to 30, with a high score representing poor quality of life [33]. The Health Assessment Questionnaire – Disability Index (HAQ-DI) will monitor changes in the physical function of participants [34]. It is a self-administered questionnaire with 20 questions designed to estimate a patient's level of upper and lower extremity functioning. The total HAQ-DI score is calculated by summing the highest score in each of the 8 domains and dividing the sum by 8, yielding a score ranging from 0 (no disability) to 3 (severe disability). Participants will be required to complete the RAQoL and HAQ-DI questionnaires at baseline, six and twelve weeks.

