## Sample size

6

The sample size calculation was based on the primary outcome measure. To detect a difference of 0.68 units (clinically relevant) in HAQ-DI [43] with 80% power and α = 0.05, 40 participants are needed in total. Adjusting for a potential 10% dropout, the sample size was determined to be 44 participants.

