## Statistical analysis

7

Data will be transferred from Castor EDC into a Microsoft excel spreadsheet, cleaned and imported into SPSS for coding and analysis. Primary outcomes will be analysed based on an ‘intention-to-treat’ principle. Descriptive statistics (M, SD, N and %) will be used to explore demographic and personal characteristics and dietary intakes of participants. Independent samples t-tests and chi-square tests will be used, as appropriate, to investigate any differences between males and females, and to examine diet adherence scores at baseline. Independent t-tests and non-parametric alternatives will be used to assess differences between the two diet groups. The threshold for statistical significance will be set to p = 0.05.; SPSS version 25 will be used for statistical analyses. Differences in outcomes for the two groups will be compared while adjusting for potential confounders such as age, medications and other lifestyle factors.

The focus groups will be audio-recorded and transcribed verbatim. According to Braun and Clarke (2013), data analysis method comprises seven steps: transcription, reading, coding, searching for themes, reviewing themes, defining themes, and finalizing [44]. The transcripts will first be read and coded by two independent investigators. Codes will be compared and discussed to reach consensus. Thematic analysis will be used to inductively code themes that appear significant. Defined themes will then be grouped into categories, as either a perceived barrier or enabler. A second analysis will follow to compare between themes across the two different intervention groups. Analysis of data will mostly be descriptive.

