## Discussion

9

Despite remarkable advancements in the pharmacological treatments of RA, other management approaches are commonly sought by individuals living with the condition [11,45]. There is a small number of randomised controlled trials and very little evidence on diet and RA. Having a better understanding of the impact of dietary interventions, as an approach for the management of RA will lead to development of dietary guidelines for this population. The MedDiet has been gaining popularity not only in the scientific literature, but also in clinical settings due to its many health benefits. While there is evidence to suggest that this dietary pattern is beneficial for inflammatory conditions, the evidence to recommend this dietary pattern for people with RA is still lacking. The proposed study aims to assess the effect of implementing a MedDiet among adults with RA in Ireland and to determine whether the MedDiet is superior to a standard healthy diet.

The MEDRA study has some limitations that need to be acknowledged. The intervention period is 12 weeks, this is a somewhat a short duration for a dietary intervention compared to other dietary interventions [46]. The sample size is small, and recruitment of study participants is conducted mainly through social media platforms so participants in the MEDRA study may represent a selected group of people with RA and potential selection bias must be evaluated. Further, while both primary outcome measures are clinically relevant, they are subjective measures and must be considered when interpreting results. Moreover, the fact that the MEDRA study is an unblinded study may introduce additional bias. The strength of this research is in its randomised controlled trial design. A trained RD is responsible for delivering both dietary interventions to ensure consistent high quality patient support. Focus group discussions at the end of the intervention will facilitate a deeper exploration into the enablers and barriers of the dietary interventions which is crucial for designing future interventions. Furthermore, the MEDRA study is carried out in collaboration with a consultant rheumatologist and, therefore, results may easily be shared with treating physicians in Ireland.

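### Two outcomes are called primary, but the trial is sized on HAQ-DI alone with one 0.05 threshold and no success rule, so the stated 5% error and 80% power do not hold together

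*Protocol article*

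**What the plan says.** Four places in the protocol article treat physical function (HAQ-DI) and quality of life (RAQoL) as primary:

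- Section 4, Outcome measures: "Primary outcome measures include physical function and quality of life".
- Abstract, Methods, after naming both as primary: "both of which will be measured using validated questionnaires at baseline, six and twelve weeks".
- Section 2.1, Study design: "The primary endpoint is an improvement in physical function and quality of life of participants over the study period".
- Section 9, Discussion: "both primary outcome measures are clinically relevant".

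Section 6, Sample size, speaks of one: "The sample size calculation was based on the primary outcome measure". It then uses a HAQ-DI difference of 0.68, 80% power and α = 0.05 to reach 40 participants, or 44 after a 10% dropout allowance. It gives no difference, SD or power for RAQoL.

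Section 7, Statistical analysis, gives the group comparison, "Independent t-tests and non-parametric alternatives will be used to assess differences between the two diet groups", and one cut-off, "The threshold for statistical significance will be set to p = 0.05". It sets no alpha split, testing order or rule on whether one or both outcomes must succeed.

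On timing, section 4.1 says "Participants will be required to complete the RAQoL and HAQ-DI questionnaires at baseline, six and twelve weeks". Table 1 labels week 6 as mid-intervention and week 12 as post-intervention. No visit is named as the primary one.

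**The concern.** The sections disagree on how many primary outcomes there are, and the error rate and power that the plan quotes depend on the answer. The 5% and 80% in section 6 describe one comparison of HAQ-DI. The primary claim described in the abstract and in sections 2.1, 4 and 9 concerns two outcomes.

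Without a success rule, the investigators could decide after seeing the data whether one significant outcome is enough. That matters more here than in many trials: the sample is small, treatment is unblinded, and both outcomes are self-reported, as section 9 acknowledges. Section 9 also says the trial is meant to determine whether the Mediterranean diet is superior, so the strength of that claim rests on how the primary test is defined.

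**Working it through.** **Inputs from the documents.** Difference 0.68 HAQ-DI units, α = 0.05, power 80%, 40 evaluable (section 6). Allocation 1:1 (section 3.1), so 20 per arm. Two primary outcomes (abstract, sections 2.1, 4 and 9). Threshold 0.05 (section 7).

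**Inputs assumed.** Two-sided tests, since sidedness is not stated. The SD and the correlation between outcomes are not given. The SD is back-solved and the correlation is varied from 0 to 0.7.

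**1. The plan's own figure.** The 40 cannot be reproduced independently without an SD. Solving for the SD that it implies:

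- Normal formula: SD = 0.68 / [(1.960 + 0.842) × √(2/20)] = 0.68 / 0.886 = 0.77.
- t-test with 20 per arm: 80% power needs a standardised effect of d = 0.909, so SD = 0.68 / 0.909 = 0.75.

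So 40 is consistent with an SD of about 0.75–0.77 for a single two-sided HAQ-DI comparison. The dropout step is 40 × 1.10 = 44.

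**2. If either outcome suffices.** With independent outcomes, each tested at 0.05, the chance of at least one false positive is 1 − 0.95² = 9.75%. This needs neither the SD nor the effect size. For correlated outcomes, from simulation of two-sided tests:

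| Correlation between outcomes | Family-wise error |
|---|---|
| 0 | 9.7% |
| 0.3 | 9.6% |
| 0.5 | 9.0% |
| 0.7 | 8.4% |

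Simulating t-tests with 20 per arm gives 9.9%, 9.3% and 8.2% at correlations 0, 0.5 and 0.7. The range is therefore about 8–10%. HAQ-DI on its own still has 80% power.

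**3. If both outcomes are required.** The error rate stays at or below 5%. Joint power cannot exceed the lower of the two individual powers. If RAQoL also has 80% power (same standardised effect, d about 0.91):

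| Correlation between outcomes | Power for both |
|---|---|
| 0 | 0.80 × 0.80 = 64% |
| 0.3 | 67% |
| 0.5 | 69% |
| 0.7 | 71% |

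The 80% for RAQoL is illustrative. With independent outcomes, joint power is 0.80 × the RAQoL power, so 60% for RAQoL would give 48% and 90% would give 72%.

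**4. If alpha is split to protect the either rule.** At 0.025 each, HAQ-DI power with 20 per arm falls from 80% to 70% (t-test) or 71% (normal formula). Restoring 80% needs 25 per arm, that is 50 evaluable, or 50 / 0.9 = 56 randomised.

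**5. Visits, as a hypothetical.** If week 6 were also tested as primary, there would be four tests: 1 − 0.95⁴ = 18.5% if all were independent. With correlations of 0–0.7 between outcomes and 0.5–0.7 between visits, simulation gives about 14–18%.

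**The case against.** Three points on the other side have force.

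First, a multiplicity rule and a primary analysis visit are often left to the analysis plan, which is not shown, and this is a condensed article. Their absence alone would be no finding. What stands regardless is that section 6 has one primary outcome where the abstract and sections 4 and 9 have two. An analysis plan could add a rule, but it would not make these statements agree.

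Second, a reader might infer that four primary tests are planned, two outcomes at two visits, and that any one of them could be declared a win. The documents do not say so. The abstract and section 4.1 state when questionnaires are completed, not when groups are tested. The 12-week design and the labels in Table 1 point towards week 12. The 14–18% is therefore an upper case that the missing primary visit leaves open, not a description of the plan.

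Third, section 2.1 joins the two outcomes with an *and* in a singular primary endpoint. Read literally, both are required and there is no alpha problem. This is a fair reading, but the section states no formal success rule, and the reading moves the shortfall to power, which section 6 does not address.

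It is also true that the power figures rest on a back-solved effect and an assumed RAQoL effect. The 9.75% for independent outcomes rests on neither.

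**Conclusion.** The concern holds as an internal inconsistency with a measurable consequence. Two outcomes are primary, the trial is sized on one, and a single 0.05 threshold is applied without a success rule. The consequence takes one of two forms:

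- Either outcome suffices: family-wise error about 8–10%, with HAQ-DI power unchanged at 80%.
- Both are required: error at or below 5%, joint power about 64–71%.

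A reader might conclude that the error rate and the power both fail. That is too strong: which one fails depends on the unstated rule. The supported statement is that the quoted 5% and 80% do not hold together for the two-outcome primary claim under either rule.

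The figures assume two-sided tests, 20 evaluable per arm and correlations from 0 to 0.7. The power figures further assume an SD of about 0.75 and an RAQoL effect equal to the back-solved HAQ-DI effect.

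**What to change.** Name HAQ-DI at week 12 as the single primary endpoint, because the sample size rests on it. Test RAQoL at week 12 second, at 0.05, only if HAQ-DI is significant. Report week 6 results for both as supportive, with estimates and confidence intervals. Align the abstract and sections 2.1, 4, 6, 7 and 9 with this.

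This sequence keeps the error rate over the two tests at 5% and leaves the planned 80% power for HAQ-DI intact with 40 evaluable participants. The chance of reaching both claims remains the joint power above, about 64–71% under the same assumptions.

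If both outcomes are to stay co-primary, state whether one or both must succeed and restate the design to match. An either rule with a 0.025 split has about 70% HAQ-DI power at 40 evaluable, or needs 50 evaluable (56 randomised) for 80%. A both rule needs the joint power stated, with an RAQoL effect, an SD and a correlation to support it.

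The preferred option needs no extra participants, but it is more than an edit of wording. RAQoL moves from co-primary to second in the hierarchy, and the protocol and registry entry need a documented amendment before outcome data are compared between groups.

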### Physical function and quality of life

4.1

The Rheumatoid Arthritis Quality of Life instrument (RAQoL) is the first patient-completed instrument specifically designed for use with people with RA. It entails 30 questions and respondents are required to indicate whether each of the questions applies to them. Scores range from 0 to 30, with a high score representing poor quality of life [33]. The Health Assessment Questionnaire – Disability Index (HAQ-DI) will monitor changes in the physical function of participants [34]. It is a self-administered questionnaire with 20 questions designed to estimate a patient's level of upper and lower extremity functioning. The total HAQ-DI score is calculated by summing the highest score in each of the 8 domains and dividing the sum by 8, yielding a score ranging from 0 (no disability) to 3 (severe disability). Participants will be required to complete the RAQoL and HAQ-DI questionnaires at baseline, six and twelve weeks.

### Diet and physical activity

4.2

Participants will be expected to complete a 3-day food diary to include 2 weekdays and 1 weekend day at three time points (baseline, six and twelve weeks) using the Libro - Food Diary & Nutritional Analysis mobile application from Nutritics [35]. The Libro mobile application will be used for logging foods and will help participants keep track of their food and physical activity. Once consent is obtained, all participants will receive a link via email to download the Libro mobile application on their mobile phones. Participants will also receive a link to access the beginner's guide to using Libro which will help them navigate through the application and learn how to add foods and exercise to their diet logs. Any challenges faced by participants will be resolved with the study RD. The 3-day food diary will be used to assess habitual diet and dietary compliance. Participants will be asked to record their intakes while using plate size measurements throughout the day to avoid recall errors. During every video consultation at baseline, six and twelve weeks, the RD will examine the food diaries to check for any missing detail or errors so that they can be amended in consultation with the participant. To check the accuracy of portion size, household measures will be used. Data from food diaries will be exported to Nutritics Diet Analysis software for analysis at baseline, six and twelve weeks. Compliance to the Mediterranean diet will be assessed using the MEDAS from the PREDIMED study [36]. Given the lack of a validated checklist that can accurately assess the adherence towards adherence to the Healthy Eating Guidelines, the authors developed an 11-item checklist based on the dietary guidelines to measure the adherence of participants in the HEG group. The Yale Physical Activity Survey (YPAS) will monitor changes in physical activity [37]. The YPAS includes questions about low intensity, high and leisure activities. The summary indices from YPAS i.e. total activity time and energy expenditure will be used to rank participants based on their activity levels (e.g. Low, moderate, high).

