### Timeline of assessments

2.4

All participants will complete three video teleconsultations meetings through Zoom or Microsoft Teams at baseline, six and twelve weeks. Participants from both groups will also receive two telephone call follow up reviews at weeks three and nine. The video calls will be 30–45 min in duration while telephone call follow-ups will be between 10 and 20 min each. All calls will be delivered by the study RD. All participants will be informed of their diet allocation group during the baseline teleconsultation and will commence the diet the following day or as soon as is feasible for a period of 12 weeks. Participant information including demographic data, smoking status, medication and supplement consumption will be collected at baseline and checked at each video teleconsultation for changes. The baseline teleconsultation will consist of a nutrition and dietetic education session whereby the study RD explains the assigned dietary pattern to participants and how they will be following it over the 12 weeks study period. During the telephone call follow-up reviews, the RD will encourage participants to set three goals that focus on improving diet quality within their assigned diet or maintaining existing positive dietary habits. These goals will be reviewed and modified as needed at follow up sessions. The RD will also monitor participants’ compliance to the assigned diet using a 24-h recall which will be administered over the telephone at weeks three and nine. Table 1 outlines the schedule of measures at each time point.

**Table 1 tbl1:** Schedule of activities/measures for participants by week of study participation.

Variable	Instrument	Time point				
		Baseline (week 0)	Follow-up (week 3)	Mid-intervention (week 6)	Follow-up (week 9)	Post-intervention (week 12)
Diet intakes	3-day food diary	x		x		x
	24 -hour recall		x		x	
Diet adherence	MEDAS	x		x		x
	Healthy Eating Checklist	x		x		x
Quality of Life	RAQoL Questionnaire	x		x		x
Physical function	HAQ-DI	x		x		x
Anthropometric measures (weight)	patient-report	x		x		x
Anthropometric measures (height)		x				
Physical activity	YPAS	x		x		x
Medications and supplements	patient-report	x				
Smoking status	patient-report	x				
Ethnicity	patient-report	x				

Definition of abbreviations: MEDAS = Mediterranean Diet Adherence Screener; RAQoL = Rheumatoid Arthritis Quality of Life; HAQ DI = Health Assessment Questionnaire- Disability Index; YPAS= Yale Physical Activity Survey.

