### Screening assessment and randomisation

3.1

Prospective participants who express interest in the study will be contacted by the study RD who will administer a screening questionnaire over the phone. Once deemed eligible, the participant will receive a participant information sheet (PIS) and a consent form to sign and return. Next, participants will be randomly allocated into either a MedDiet group or HEG group using a permuted block randomisation scheme with 1:1 ratio allocation [32]. Randomisation is conducted by a statistician at the University of Limerick, who is not involved in the conduct of the RCT. Next, participants will be invited to complete the online questionnaires. A CONSORT flow chart of participants through the study is provided in Fig. 1.

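### YPAS is collected to follow change in physical activity, but the only stated use of its continuous indices is to rank participants into broad levels, which shows change poorly.

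*Protocol article*

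**What the plan says.** Section 4.2 of the Protocol article (Diet and physical activity) states the purpose: "The Yale Physical Activity Survey (YPAS) will monitor changes in physical activity". Table 1, in section 2.4, schedules YPAS at baseline, week 6 and week 12. Two sentences after the purpose, section 4.2 gives the only use it states for the summary indices: "total activity time and energy expenditure will be used to rank participants based on their activity levels (e.g. Low, moderate, high". It gives no cut-offs and does not say whether the levels are fixed or relative to the sample.

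Section 7 (Statistical analysis) plans an adjusted comparison: "Differences in outcomes for the two groups will be compared while adjusting for potential confounders such as age, medications and other lifestyle factors". Physical activity is not named there, and neither its form nor its time point is given. The physical-function outcome is the HAQ-DI (section 4.1), and allocation is 1:1 in permuted blocks (section 3.1).

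**The concern.** The purpose is change over three visits, while the stated use is a coarse ordering of people. Both indices are continuous and already scheduled, so the ordering gives up information that costs nothing to keep.

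Activity is worth seeing clearly in this trial. It is a plausible co-intervention for an outcome that measures upper and lower limb function. Sections 2.1 and 9 say the trial is unblinded, and section 9 concedes that both primary outcomes are subjective. The food-diary app also logs exercise, so activity may change during the study. If the arms differ on HAQ-DI, readers will ask whether activity moved differently by arm, and YPAS is the instrument in place to answer. At stake is how well that question can be answered, and how well a chance baseline imbalance in activity could be adjusted for.

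**Working it through.** **Plan figures.** The article states no figure for YPAS, so there is none to reproduce. The only design figure used is the 40 evaluable participants in section 6, taken as 20 per arm. Everything else below is an assumption: a standard normal index, tertile cut-points and the baseline-to-follow-up correlations.

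**1. Variance kept by three equal groups.** The tertile cut-points of a standard normal are ±0.4307. The mean of an outer third is φ(0.4307)/(1/3) = 1.0908, and the middle third has mean 0. Variance kept = (2/3) × 1.0908² = 0.793, or about 79%. This describes a single visit; it is not a measure of power for change.

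**2. Fixed bands: who changes level?** Suppose everyone rises by s SD and the cut-points stay at ±0.4307. The share staying in the same band is Φ(−0.4307 − s) + [Φ(0.4307 − s) − 1/3] + 1/3; the middle term is zero if 0.4307 − s falls below −0.4307.
- s = 0.25: 0.248 + 0.238 + 0.333 = 0.82
- s = 0.5: 0.176 + 0.139 + 0.333 = 0.65
- s = 0.8: 0.109 + 0.023 + 0.333 = 0.47

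So after a rise of half an SD, about two-thirds of people show no change in level.

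**3. Fixed bands: power to see a between-arm shift in activity.** In a simulation with 20 per arm and 2,000 runs per scenario, one arm was shifted at follow-up. A t-test on continuous change was compared with a Mann-Whitney test on change in band. Ranges cover baseline-to-follow-up correlations of 0.5 to 0.8.

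| Shift in one arm | Continuous change | Change in band |
|---|---|---|
| 0.25 SD | 11–24% | 9–12% |
| 0.5 SD | 34–69% | 22–37% |
| 0.8 SD | 71–97% | 46–67% |

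The continuous column agrees with a hand check. The SD of change is √(2(1 − r)). At r = 0.5 this is 1, so 0.5/(1 × √(2/20)) = 1.58 and power ≈ Φ(1.58 − 1.96) = 0.35, against 0.335 simulated with the t-test. At the 0.5 SD shift, the relative fall in power from banding is 1 − 0.216/0.335 = 36% at r = 0.5 and 1 − 0.370/0.687 = 46% at r = 0.8.

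**4. Ranks relative to the sample at each visit.** Adding the same constant to every value leaves the order unchanged, so a common increase leaves no trace. A shift that differs by arm can still alter ranks, but its size in time or energy is lost.

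**5. Does this reach the HAQ-DI comparison?** The unadjusted comparison does not use YPAS, so banding cannot alter it. Baseline activity matters only if it is among the lifestyle factors in section 7. In that case a banded covariate leaves within-band imbalance uncontrolled.

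**The case against.** The strongest reply is that this is a condensed article. Ranking is one stated use, its labels carry an e.g., and nothing says the continuous values are discarded. How a supporting measure is summarised may sit in an analysis plan that is not shown. That stands against any claim that the trial cannot show activity change. It does not dispose of the point, because the article does state a method, and that method fits poorly with the purpose stated two sentences before it.

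A reader might also infer that a hidden activity shift confounds the physical-function result. The documents do not support this. Arms are randomised, so activity change after baseline is a co-intervention or mediator. It bears on how a HAQ-DI difference is attributed to diet, and adjusting for it could remove part of the diet effect. An increase common to both arms does not bias the difference between them. The exercise log adds no imbalance by design, since all participants receive the app.

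Two further limits are fair. The complete loss of a common shift holds only if ranks are recomputed within the sample at each visit; with fixed bands, about 35% of people change level after a 0.5 SD rise. And the article nowhere says that banded YPAS enters the HAQ-DI model.

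**Conclusion.** The point holds as a minor mismatch between purpose and method. Under either reading of ranking, the stated use shows change in activity less well than the continuous indices would. With assumed fixed tertile bands, a normal index and 20 per arm, power to detect a 0.5 SD between-arm shift in activity falls from 34–69% to 22–37%, and about 65% of people stay in their band after a uniform 0.5 SD rise. These figures illustrate the loss: the article gives no cut-offs and no distribution, and a skewed index would change them. Part of the power gap also reflects comparing a t-test with a rank test on heavily tied values.

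The consequence is limited to a weaker description of activity by arm and, conditionally, weaker baseline adjustment. No bias in the unadjusted HAQ-DI result follows.

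**What to change.** Replace the ranking sentence in section 4.2 with wording such as: *YPAS total activity time and energy expenditure will be analysed as continuous values and reported as change from baseline at weeks 6 and 12 by arm, with a 95% CI for the difference between arms (log-transformed if skewed). Low, moderate and high levels, with stated cut-offs, will be used for description only.*

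In section 7, say whether baseline activity is one of the lifestyle factors. If it is, enter only the continuous baseline value, and do not adjust for activity measured after randomisation.

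The cost is a change of wording, a little more analysis and perhaps a transformation. No new data are needed, since YPAS is already scheduled at all three visits.
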